**Fig 1 pone.0356055.g001:**
[figure not shown]
EMPATH study schedule (SPIRIT guidelines).

**Fig 2 pone.0356055.g002:**
[figure not shown]
Study timeline. After the baseline assessment (T0), eligible participants are randomized (stratified by neglect severity) and undergo a 10-day treatment over two weeks. Follow-up assessments occur within one week and one month of finishing treatment (T1, T2, respectively).

### Study population

Participants with right-hemisphere stroke will be recruited from several sites in Nova Scotia: the Acquired Brain Injury Program at the Nova Scotia Rehabilitation and Arthritis Centre, the Early Supported Stroke Discharge Team, and the Acute Stroke Program of the Valley Regional Hospital. Recruitment is also open to the community. Participants may be referred to the study by a clinician or directly recruited from the community by the research team through advertisement and stroke support group visits. Study staff will visit participants for training and assessments, either at their home or in inpatient units, depending on each participant’s current admission status. For participants who enroll while in an inpatient unit but are discharged before completing the study, a hybrid approach will be implemented, allowing them to complete the remaining aspects of the study at home.

#### Inclusion criteria.

To be eligible for the baseline assessment, participants must: 1) have experienced a right-hemisphere stroke; 2) be willing and able to hear about the study and consent to participate; 3) be medically stable; 4) have self-reported normal to corrected-to-normal visual acuity; 5) be able to point with the unaffected limb; and 6) reside within a two-hour radius of Halifax, which ensures accessibility of resources and proximity to the research team. The baseline assessment will be used to confirm symptoms of neglect before randomization into the treatment phase. Neglect will be defined by impaired performance on at least 2 subtests of the BIT [42] and/or at least two ratings of “often” on the Caregiver version of the Halifax Neglect Impact Scale, indicating frequent impacts of neglect symptoms on ADLs.

#### Exclusion criteria.

Participants will be excluded if they have any other existing neurological disorder (e.g., dementia, multiple sclerosis, epilepsy).

### Sample size

The sample size for this study was determined using the Superpower [46] package in R 4.5.3 software. The primary outcome measure for this study is the total score on the Star Cancellation conventional subtest of the BIT, and the primary analysis strategy will be analysis of covariance (ANCOVA). We used the threshold for a clinically significant effect size measure proposed by Székely et al. (d = 0.61) [47]. A test-retest correlation during treatment of *r* = 0.63 (R^2^ = 0.40), was estimated using raw data from the supplementary materials of Vilimovsky et al. [48], using their results from the Bells cancellation test as a reasonably close proxy. Thus, assuming an alpha of 0.05, 80% power, d = 0.63, and a R^2^ for covariates of.40 requires a sample size of 27 per group. Because of local feasibility concerns when studying this population, we believe it is unlikely it would be possible to collect more than 25 participants per group. Thus, we lowered our threshold for statistical power to 70%, which requires a minimum sample size of 21 per group as our target. Although 80% power is commonly treated as a benchmark, power between 70% and 90% remains within accepted norms [49]. Consistent with recommendations that sample size in constrained clinical populations should reflect the maximum feasible recruitment under real-world conditions [50], our target sample also takes into consideration practical feasibility. The R script with our power analysis is included in the supporting information materials S3 File.

### Randomization

Covariate-adaptive randomization, as described by Sella et al. [51], will be used to assign participants to treatment conditions. Randomization is stratified based on neglect severity, assessed using the BIT [42]. Specifically, participants will be considered as having “mild” neglect if they fail fewer than 3 subtests on the BIT, or when only functional symptoms are reported. Participants will be considered as having “moderate to severe” neglect when they fail 3 or more subtests on the BIT. Severity classification will be completed by a blinded assessor. Participants will be assigned to one of two groups in a manner that balances neglect severity between groups, to control for potential baseline differences in symptom severity. Randomization will be conducted by a member of the research team who is not involved in data collection or analysis and provided to the assigned Trainers immediately before the “training” visit (i.e., home or inpatient visit #2).

### Blinding

The Trainer assigned to each participant will not be blinded to the treatment condition, as they are responsible for training participants on the protocol and they will handle the goggles (i.e., 5- or 15-degree). To minimize trainer influence, all trainers receive standardized training from the same supervisor and must demonstrate competence before interacting with participants. Trainers follow detailed, manualized protocols to ensure procedural consistency across both trainers and sessions, and training tasks are fully computerized with automated instructions and feedback. These steps substantially reduce the potential for bias. Assessors will remain blinded to the treatment condition, and participants will not be informed of which treatment they are receiving. As previous research has shown that 15-degree goggles induce significantly larger after-effects than 5-degree goggles when using PTM, 5-degree goggles will be used as an “active control” [39]. Using 5-degree deviating goggles as an “active control” rather than the typical sham (i.e., clear) comparator preserves the double-blind design of the present study. Upon completion of the study, both participants and their Assessors will be asked to indicate which treatment condition they believe was assigned.

### Intervention

#### Equipment.

For PTM training, participants will receive Welder goggles fitted with Fresnel prisms inducing a rightwards optical shift of either 5- or 15-degrees (Insight Optometry Group, Halifax, Canada). The PTM software will be administered using a case-protected 9^th^ generation Apple iPad (64GB;10.2-inch LED-backlit multi-touch display with IPS technology; resolution: 2160 x 1620 pixels; iPad width: 21 cm). A wireless QWERTY computer keyboard (OMOTON Ultra-Slim Wireless Bluetooth) will be used with the iPad.

#### Experimental condition.

PA will be administered using the PTM software, which displays pointing targets, records touch locations and provides feedback on accuracy and response time (in milliseconds). Participants are seated in front of an iPad, centered with the screen, at a distance allowing them to touch the screen with a slightly bent arm. While wearing 15-degree rightward-deviating prism goggles, participants are instructed to touch a target bull’s eye held by a cartoon mole on an iPad, as quickly as possible. To initiate each trial, participants hold down the spacebar on the QWERTY keyboard with their dominant hand. When the mole appears in one of 9 locations on a 3x3 grid, participants release the space bar and attempt to touch the target as quickly as possible. After each response, the mole provides visual and auditory feedback on accuracy and response time.

To calculate the initial target presentation time for the exposure task for each participant, 10 practice trials will be administered without the use of prism goggles. Practice trials may be repeated as necessary. The mean response time over last the 10 practice trials will be used as the initial target presentation time for the exposure task. The exposure task, lasting approximately 15 minutes (depending on response speed), involves 117 trials in total (13 trials for each of the 9 target locations). Between tasks (e.g., practice trials and exposure task), written and audio-recorded instructions are provided to guide participants through each step (e.g., “put goggles on”).

The PTM software uses an algorithm that adjusts the target presentation speed based on individual performance, promoting ballistic movements and minimizing self-correction in pointing movements. The software uses an algorithm to ensure performance accuracy is maintained by manipulating target presentation time based on the participants’ performance. To further encourage ballistic pointing movements and enhance engagement in the task, participants receive feedback when they reach a new timing level. The PTM software records participants’ pointing errors in degrees of visual angle (DVA).

Participants will be asked to complete 10 training sessions over a two-week period. To enhance and monitor treatment adherence, participants will be asked to fill out daily training logs, and their assigned Trainer will make weekly check-in phone calls. For additional support, participants will have access to a phone number and email for troubleshooting. The PTM intervention will be administered in addition to usual care.

#### Active control condition.

The active control condition follows the same procedure as the experimental condition, with one key difference: participants in the control group wear 5-degree rightward-deviating goggles while completing the exposure task (i.e., PTM). Participants complete the exposure task (PTM) while wearing these 5-degree goggles, providing a mild visual shift that serves as an “active control” to maintain double-blind conditions without delivering the therapeutic effect expected from the 15-degree shift.

### Data collection and management

All research staff, including Assessors and Trainers, will receive standard training on data collection methods from the same supervisor. Study personnel consist of graduate-level clinical psychology students and supervised undergraduate students. All students must demonstrate competence in all tasks required for the “Trainer” and “Assessor” roles (e.g., administration of assessments) prior to data collection. Study personnel follow manualized protocols throughout the study.

Consent forms, participant demographics and health history, training logs, and data summaries will be securely stored using the Research Electronic Data Capture (REDCap) system hosted by Nova Scotia Health. Each participant will be assigned a unique identification number to ensure data de-identification. Other electronic data files will be stored on password protected computers or saved on a secure lab network behind a firewall. Access to electronic data is restricted to authorized personnel. Paper files will be stored in a locked laboratory with access limited to authorized personnel. If a participant withdraws from the present study or their participation ends early, all data collected up to the date they withdraw their consent and/or their study participation ends, will be maintained in the study records to be included in the study related analyses.

### Measurements

#### Screening data.

Screening data will be collected with a health history questionnaire after obtaining informed consent and before the baseline assessment. The questionnaire includes demographic information (e.g., age, gender, education level) and health history, such as any relevant health and psychiatric conditions. Additionally, the Stroke Impact Scale Short Form (SF-SIS) [52] will be administered to assess stroke impact across various dimensions such as mobility and ADLs.

#### Baseline data.

After initial screening, a baseline assessment (T0) will be conducted. The purpose of the baseline assessment is to describe the cognitive profile of the sample. This assessment includes: confrontation visual field testing, Montreal Cognitive Assessment (MoCA) [53], a shortened version of Judgement of Line Orientation (JLO) [54,55], Digit Span (forward and backward) [56], Trail Making Test (A and B) [57], abbreviated Landmark Task [58], and the Attention Motor Task (i.e., a reaching task designed to characterize neglect subtype) [59].

#### Primary outcome.

The Star Cancellation conventional subtest of the Behavioural Inattention Test (BIT) [42] will serve as the primary outcome and will be measured at three time points: T0 (baseline), T1(immediately post-intervention), and T2 (one-month post-intervention). This measure assesses changes in performance from pre- to post-prism training and was selected as the primary outcome due to its greater sensitivity in comparison to other paper-and-pencil tasks [42,60]. The Star Cancellation subtest requires patients to cancel small stars among distractors on a page that is placed in their center of body. The scores range from 0–54, with scores at or above 52 as the “acceptable range”. The subtest has excellent test-retest reliability [61]. Additionally, compared to other measures of neglect, previous research has found that the Star Cancellation subtest is the best predictor of functional outcome as assessed by an ADL scale [62].

#### Secondary outcomes.

Secondary outcomes will include the remaining conventional subtests of the BIT [42], three behavioural BIT subtests (menu reading, article reading and picture scanning) [42], one subtest of the Eschenbeck Standardized Activity of Daily Living Test (SADL; *filling out a form*) [63], the Halifax Neglect Impact Scale (self- and caregiver-reported measures assessing the frequency and impact of neglect symptoms on ADLs), the Hospital Anxiety and Depression Scale [64] and the Fatigue Severity Scale [65]. Each of these secondary outcomes will be administered at all three assessment time points.

Feasibility and acceptability data will also be collected at T1 (i.e., within one week of training) via a Patient Exit Interview, using a modified version of the Intrinsic Motivation Inventory [66] which includes 38 Likert scale questions and 8 open-ended questions about usability and enjoyment of the PTM software.

To measure PA after-effects, a modified Proprioceptive-and-Visual Straight-Ahead (mPVSA) task (described below) will be administered immediately after each training session.

#### Measurement of after-effects.

An mPVSA outcome task will be used to assess after-effects before and after each treatment session, without the use of prism goggles. The mPVSA task was developed specifically to accommodate the home-based nature of the protocol, eliminating the need for an occlusion board, which is often unavailable in home and rehabilitation settings. During the mPVSA task, participants will view a cartoon bull’s eye at one of two untrained locations on the central horizontal row of the 3x3 grid displayed on an iPad screen. This setup allows for the examination of the generalization of after-effects to untrained spatial locations. Participants will be asked to memorize the target location and then press the spacebar on a QWERTY keyboard with the index finger of their dominant hand. When the spacebar is pressed, the target disappears behind a pixelated colour screen. Once the colour screen disappears, participants will use the same index finger to touch the screen where they last saw the target. The pixelated colour screen serves as a visual mask, supporting memory-guided pointing without the need for an occlusion device. Auditory cues will confirm the participant’s touch response for each trial. Each session will include ten trials administered immediately before and after the PTM exposure task, with relevant instructions provided both in writing and as audio recordings. Mean after-effects correspond to the difference in endpoint accuracy (in DVA) from pre- to post-PTM. Touch location on the iPad screen is recorded in real time. As the task is self-administered, potential sources of measurement error include premature responses and mis-registered screen touches which are mitigated through auditory/visual instructions and feedback. Additionally, posture and viewing position differences between participants are minimized through a standardized set-up completed by the Trainer during the initial session. The Trainer tapes the iPad position on the table and provides a pre-cut string so the participant can measure the appropriate viewing distance from the iPad before each training session. Protocol adherence is evaluated at the end of the two-week training period.

### Statistical analyses

Given the heterogenous nature of neglect, deficits may not be captured by a single task; therefore, a battery of subtests was selected to assess functioning across multiple areas (e.g., functional and paper-pencil tasks). Subtest-level analyses will capture deficits and improvements across different areas of functioning. Note that the study has a single primary outcome (Star Cancellation subtest of the BIT); thus, the strongest evidence of the trial’s efficacy will be determined from this a-priori outcome. Secondary outcomes will have weaker evidential value but may remain useful for future meta-analyses and to inform future research.

To assess the effectiveness of the PTM intervention on neglect severity over time, data will be analyzed using analysis of covariance (ANCOVA) using generalized linear modelling with the glm() function in R software. We are interested primarily in two mean differences: (a) changes from pre-PTM (T0) to immediate post-PTM (T1) and (b) changes from pre-PTM (T0) to 1-month post-PTM (T2). Because mean differences from T1 to T2 are assuredly smaller than comparisons to baseline, our study would be underpowered to detect them, so we have elected to calculate only the primary comparisons of interest. In the first ANCOVA analysis, the outcome will be at T1, and predictors will include T0 scores and time post-stroke as covariates, and Condition (5-degree vs. 15-degree goggles) as a between-subjects factor. In the second ANCOVA analysis, the outcome will be at T2, T0 scores, time post-stroke, and follow-up assessment timing will be used as covariates, and Condition will again be a between-subjects predictor. In the second analysis, follow-up assessment timing will be included to assess whether differences in timing for post-treatment assessments impacts treatment outcomes.

The primary outcome (Star Cancellation conventional subtest of the BIT) produces integer data and likely has a left skewed distribution, with an inflation of perfect scores. Thus, analyzing the data with methods suitable for count data may provide a better fit to the data. Since most commonly available methods are intended for use with right-skewed data, the scores will be reflected (i.e., re-scaled by subtracting 54 then taking the absolute value of scores) such that the scale will indicate the number of misses instead of the number of hits, producing right-skewed data. Because the population distribution of scores is unknown, our approach will be to analyze the data two ways (a) with a gaussian distribution and an identity link, which is equivalent to a standard ANCOVA and (b) assuming a negative binomial distribution with a log link, which assumes a right skewed distribution with overdispersion (i.e., mean > variance). We will compare the Bayesian Information Criteria (BIC) between the two models, and if the ΔBIC is > 2.0 we will prefer the model with the smaller BIC [67]. If the change in ΔBIC is inconclusive, we will prefer the gaussian (i.e., normal) model because it is more parsimonious. Analyses on primary and secondary outcomes will generally follow the same procedures, excepting that negative binomial models will not be run on outcomes unsuitable for such approaches (e.g., non-integer data). We will report unstandardized adjusted mean differences and the change in ΔR^2^ values when adding condition as a predictor in a second step after covariates as effect sizes. Technically-minded readers can refer to the R script posted in our supporting information materials S3 File for further details of how analyses will be conducted.

To examine feasibility and acceptability, descriptive statistics and mean ratings from participant exit interviews will be examined. Additionally, the number of completed intervention sessions will be tallied for each participant, and the mean proportion of treatment session completion will be calculated. The protocol will be deemed feasible if at least 80% of treatment sessions are successfully completed across participants.

To examine the impact of after-effects, a single average score over the two weeks of prism adaptation will be calculated. Then, we will examine the relationship between these mean after-effects scores and condition using an unequal-variances t-test. We will also explore the Pearson correlation between mean after-effects scores and the primary outcome.

An intention to treat analysis will be completed. We will also examine outcomes of participants who complete at least 80% of training and assessment components. Given the nature of our follow-up procedures, we expect low dropout. If missing data < 5%, listwise deletion will be used (complete cases) as when there is minimal missing data, more advanced strategies generally perform equivalently to listwise deletion [68]. If there is substantial missing data, it will be handled using multiple imputation using the Jomo [69] and mitml [70] packages in R software. In such a case, we will evaluate whether missing data is associated with any measured variables to incorporate into the missing data model.

All protocol deviations will be documented and reported to the principal investigator. Deviations that could affect participant safety will be promptly communicated to the ethics board. All deviations will be reviewed to assess impact, and corrective and preventative actions will be implemented as necessary to minimize recurrence.

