To support the future clinical implementation of PTM, the primary objective of the present study is to examine PTM’s effectiveness in reducing neglect symptoms as measured by the Star Cancellation task of the Behavioural Inattention Test (BIT) [42]. Short-and longer-term effectiveness will be examined in terms of symptom reduction (i.e., does the PTM PA protocol improve neglect symptoms over time?). We hypothesize that participants who complete 10 sessions of PTM PA treatment using 15-degree rightward-deviating goggles will show a greater reduction in the severity of neglect symptoms immediately after training and at one-month follow up, compared to participants using the PTM protocol with 5-degree deviating goggles.

Secondary objectives include (1) examining treatment effects across additional neglect measures, as well as measures of ADLs, (2) evaluating feasibility and acceptability, (3) examining the magnitude of PA after-effects and the relationship between these effects and neglect severity, and (4) exploring changes in psychological outcomes. First, we will examine whether the 15-degree PTM condition leads to broader improvements in neglect symptom severity across additional neglect assessments, as well as improvements in ADL functioning over time. Second, we will evaluate the feasibility and acceptability of using the iPad-based PA treatment in both inpatient and community settings. Feasibility will be assessed based on compliance with the treatment protocol and schedule, while acceptability will be evaluated through patient feedback. PA after-effects (mean difference in degrees of visual angle from pre- to post-PTM) will be measured after each treatment session. We will examine whether the 15-degree condition produces larger after-effects compared to the 5-degree condition. Additionally, we will investigate whether the magnitude of PA after-effects predicts neglect severity. The relationships between neglect severity and psychological variables, including anxiety, depression, and fatigue, as well as changes in these psychological outcomes following participation in the PTM protocol will also be explored. Although fatigue, anxiety, and depression are prevalent post-stroke [43,44], their association with spatial neglect remains underexplored, and these secondary analyses will provide insight into the broader impact of PTM and whether improvements in neglect symptoms may be associated with changes in psychological outcomes and fatigue severity.

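### One primary outcome but two primary comparisons (T1 and T2) with no success rule in the article: error exceeds 5% if either counts, and power falls below the stated 70% if both must succeed

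*Protocol article*

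**What the plan says.** All references are to the protocol article.

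- **Statistical analyses, on the outcome:** "Note that the study has a single primary outcome (Star Cancellation subtest of the BIT"). The section adds that the strongest evidence of efficacy will come from this outcome and that secondary outcomes carry less weight.
- **Statistical analyses, on the comparisons:** "We are interested primarily in two mean differences: (a) changes from pre-PTM (T0) to immediate post-PTM (T1) and (b" is the change from baseline to one month (T2). The section calls these two the primary comparisons when it explains why T1 to T2 is not analysed. Each has a separate ANCOVA with its own Condition effect. The T2 model also adjusts for follow-up timing.
- **Introduction, hypothesis:** the 15-degree group is expected to show a greater reduction in neglect severity "immediately after training and at one-month follow up".
- **Sample size:** the outcome is the Star Cancellation total score, "and the primary analysis strategy will be analysis of covariance (ANCOVA"). The calculation is made "assuming an alpha of 0.05, 80% power, d = 0.63" and a covariate R² of 0.40, and "requires a sample size of 27 per group". For feasibility, "we lowered our threshold for statistical power to 70%, which requires a minimum sample size of 21 per group as our target".

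The Primary outcome section lists T0, T1 and T2 as measurement times and does not single out T1 or T2.

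**The concern.** One outcome variable tested at two time points gives two tests of the treatment effect. Having a single primary outcome therefore does not settle multiplicity. The reader also needs to know which test decides the trial, or how the two combine, and the article does not say.

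The gap matters because the remaining design figures belong to a single test. Alpha of 0.05 and power of 70% describe one contrast at one time point. Under an either-test rule the 5% no longer holds. Under a both-tests rule the 70% no longer holds. With no rule on record, the more favourable time point could also be put forward once results are known.

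**Working it through.** **Step 1. Reproduce the plan's own figure.** Inputs from Sample size: alpha 0.05, R² = 0.40, equal groups, d given first as 0.61 (the "threshold for a clinically significant effect size measure proposed by" a cited study) and later as 0.63. Sidedness is not stated. Method: noncentral t with ncp = d/√(1 − R²) × √(n/2) and df = 2n − 3 (one covariate).

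- d = 0.61, n = 21: ncp = 0.61/√0.60 × √10.5 = 2.55, df = 39, two-sided power 70.2%.
- d = 0.61, n = 27: ncp = 2.89, df = 51, two-sided power 81.0%.
- The smallest n is 21 for 70% and 27 for 80%, exactly as stated. With d = 0.63 it is 20 and 25.
- One-sided testing with d = 0.61 would need only 16 and 21.

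So the stated sizes match **one** two-sided test at 0.05 with d = 0.61. They contain no allowance for a second test.

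**Step 2. Correlation between the T1 and T2 statistics.** The article does not give it, so it is an assumption and is varied. One anchor is available: if the article's test-retest r = 0.63 applied to every pair of visits, the baseline-adjusted correlation would be (0.63 − 0.63²)/(1 − 0.63²) = 0.2331/0.6031 = 0.39.

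**Step 3. Error rates with no treatment effect, each test two-sided at 0.05.** With (Z1, Z2) bivariate normal with correlation ρ:

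- either = P(|Z1| > 1.96 or |Z2| > 1.96). At ρ = 0 this is 1 − 0.95² = 9.75%.
- both = 0.05 + 0.05 − either.
- either, favouring 15 degrees = P(Z1 > 1.96 or Z2 > 1.96), against 2.5% for one test.

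| ρ | Either | Either, favouring 15° | Both |
|---|---|---|---|
| 0 | 9.75% | 4.9% | 0.25% |
| 0.39 | 9.35% | 4.7% | 0.65% |
| 0.5 | 9.1% | 4.5% | 0.9% |
| 0.7 | 8.35% | 4.2% | 1.65% |
| 0.75 | 8.1% | 4.05% | 1.9% |
| 0.8 | 7.8% | 3.9% | 2.2% |
| 0.9 | 7.0% | 3.5% | 3.0% |
| 1 | 5.0% | 2.5% | 5.0% |

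Simulating the two planned Gaussian ANCOVAs with 21 per group (15,000 runs each) gave either-test rates of 9.3%, 8.8% and 7.8% at ρ = 0.39, 0.6 and 0.8, in line with the formula.

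**Step 4. Power if both tests must be significant.** Assume 70% for each test, so that each statistic exceeds its critical value with probability 0.70. Joint power is then Φ₂(z, z; ρ) with z = Φ⁻¹(0.70) = 0.524:

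| ρ | Joint power |
|---|---|
| 0.39 | 54% |
| 0.5 | 56% |
| 0.7 | 59% |
| 0.8 | 61% |

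**Step 5. What a correction would cost.** Splitting alpha (0.025 per test) holds the familywise error at or below 4.9%. Power per test at 21 per group falls from 70.2% to 59.0% (d = 0.61), or from 72.9% to 62.1% (d = 0.63). Restoring 70% needs 26 per group (25 if d = 0.63), at or above the 25 that the Sample size section regards as the realistic ceiling. A fixed test order keeps the familywise error at 5% and leaves 21 per group unchanged.

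**The case against.** The strongest reply is that the article never says a win at either time point is enough. Its only stated hypothesis joins the two time points with *and*. Read as requiring both, the false-positive rate is about 0.9-2.2% at correlations of 0.5-0.8, so nothing is inflated. This stands. A reader might infer that the plan carries an 8-9% chance of a false efficacy claim, and the document does not support that as a flat statement. The figure needs an either-test rule and a correlation of about 0.5-0.75, neither of which is stated. It also counts significant results in both directions, including those favouring 5 degrees; a false claim for 15 degrees is about 4-5%.

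A second reply is that alpha of 0.05 appears only in the sample size, and that a rule may sit in a separate analysis plan or in the supporting R script, neither of which is shown. This stands too: the absence of a multiplicity rule would not be a finding on its own. The point rests on what the article itself fixes, namely one primary outcome, two comparisons both called primary, and a sample size for one test.

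A third reply is that nothing ranks T1 above T2, since the Introduction asks about both short- and longer-term effectiveness. This is correct. Several rules would be valid, and the choice belongs to the sponsor.

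The *and* reading does not rescue the plan, however. It only moves the problem from the error rate to the power.

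**Conclusion.** The concern holds in conditional form. The article names two primary comparisons of one outcome, gives no success rule, and supports them with a calculation for a single test. Neither reading agrees with both stated design figures:

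- **Either counts:** two-sided familywise error is above 5% at every correlation below 1, at most 9.75%.
- **Both required:** error is held, but power is clearly short of 70%. The target had already been lowered from 80% on feasibility grounds, so the further loss matters.

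These sizes rest on an assumed correlation between the T1 and T2 statistics, two-sided tests at 0.05 and approximate normality. The joint power also assumes 70% at each time point, that is, the same effect at T1 and T2 and no loss to follow-up. The conclusion that a rule is needed does not depend on the exact correlation.

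**What to change.** State the success rule in the protocol (and in the analysis plan, if there is one) before any results by group are known. The article says data collection is ongoing, so there is still time.

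- **Cheapest option, a fixed sequence.** Name one time point, for example T1, as the sole primary test at two-sided 0.05. Test the other confirmatorily at 0.05 only if the first is significant; otherwise report its estimate and confidence interval descriptively. State that the 70% power refers to the first test alone. This takes one or two sentences and no extra participants. The downside is that no confirmatory claim can be made at the second time point if the first fails.
- **If both time points are required,** say so and replace the 70% with the joint figure, giving the correlation assumed.
- **If either is to count,** split alpha and restate power per test (about 59% at 21 per group with d = 0.61).

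In the same edit, state that the test is two-sided and reconcile the two values of d, since only 0.61 reproduces 27 and 21 exactly.
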